## **Background+ relevance (max ½ A4, shorter preferred)**

### **a. Hypothesis**

Patients can receive prolonged anticoagulant therapy after a first venous thrombotic event to prevent recurrence, although at the cost of bleeding. Therefore it is crucial to estimate an individual's risk for recurrence, to personalize anticoagulant therapy and minimize bleeding risk. Surgery is a major risk factor for the development of venous thrombosis (VT). For this reason, routine thromboprophylaxis is strongly recommended around major surgery. Although the risk of a first VT after surgery is studied extensively, there is less information about the risk to develop a recurrent VT in patients with a history of VT who need to undergo surgery. Some studies report a high risk of recurrence; for example, one study reported that despite mechanical and pharmacological anticoagulant treatment with warfarin, patients with a history of VT who underwent a lower limb joint replacement had a relative risk of 6.3 (95%CI 2.3 to 17.5) at 90 days for recurrent VT compared with individuals that had no history of VT. Another study in patients undergoing colorectal surgery (for any cause) reported that patients with a history of VT had a 7.6-fold increased risk for recurrence (95%CI 5.1 to 11.32) compared to those without a history of VT, despite prophylactic therapy. As far we know, only one study addressed whether patients with previous venous thrombosis are at increased risk of a recurrent event, while undergoing surgery compared with such patients who do not have surgery. In that study authors observed that patients with VT who underwent surgery had a 3-10 fold increased risk of a recurrent event up to 92 days post dismissal as compared with patients with VT who did not undergo surgery over a same follow-up time. However, authors were not able to distinguish those who received thromboprophylaxis from those who did not receive thromboprophylaxis and could also not distinguish between various types of surgery.

Since many patients with a history of VT undergo surgery, and the scarcity of studies that have been performed on this issue, we decided to research the risk of recurrence in these patients to guide physicians on prescribing anticoagulant medication.

### **b. Objective**

1. To estimate the absolute risk of recurrent VT in patients with a history of VT who undergo various types of surgery.
2. To identify risk factors for recurrent VT in these patients.

## **2. Study design**

### **a. Population description (inclusion/exclusion criteria)**

For this study we will use data from the MEGA follow-up study. 4731 patients with a first venous thrombosis were followed over time for recurrent venous thrombosis until 2008-2009. Information on the occurrence of a recurrent event was collected by means of a short questionnaire or patients were contacted by phone. Detailed information about the recurrent event was retrieved from questionnaires, anticoagulation clinics, treating physicians or cause of death statistics. At the end of study about 700 cases with a recurrent venous thrombosis were identified.

Participants completed a questionnaire on putative risk factors for recurrent venous thrombosis (including [type of] surgery). Despite this information, we will not use this data as information bias (recall bias) is likely to be present. The MEGA follow-up database has been linked to the Central Bureau of Statistics (CBS) database of the Netherlands with information on all surgical procedures (including dates) for all individuals that participated in the study. We will use these data to identify patients who underwent a surgical procedure during the period of interest.

### **b. Exposure (independent variable)**

We are interested in all surgical procedures (i.e. orthopedic, non-orthopedic, gynecological, urological, abdominal, vascular, neurosurgical, etc), both daycare procedures and operations whereby patients are hospitalized for one or more days (see table under 4b), and we will differentiate between major and non-major surgery. These procedures are identified using ICD-coding that is registered in the CBS database.

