### **3. Statistical analysis**

#### **a. Methods**

Follow-up time will be calculated from the start of follow-up (i.e. 1. from stop date anticoagulant treatment after first VT and 2. from date of first VT onwards as a sensitivity analysis) until the end of follow-up (end of study, dead, recurrent event or loss to follow-up, whichever occurs first). The time window of surgery exposure for each individual is defined as 3-months from the surgery date. The total follow-up time in which patients are not exposed will be calculated as the total follow-up time minus the exposure time. As a sensitivity analysis, we will vary the time window of exposure because it is not known for how long the VT risk is increased after surgery. Therefore we will also consider a 1-month, 6-month and 1-year time window after surgery. We will calculate cumulative incidences for recurrent venous thrombosis for the exposed time windows and incidence rates by dividing the number of events by person-time for the exposed and the unexposed time periods.

Cox-proportional hazards modeling (with a time-dependent co-variate [surgery]) will be used to calculate a hazard ratio for developing recurrence. Also, we will estimate Hazard Ratios for several types of surgery on recurrence risk, and adjust for important confounders. Absolute risks for

recurrent VT will be calculated for several types of surgery (for all different time windows after exposure).

To identify high risk groups, we will perform a matched case-control study within this cohort. Cases are patients with a recurrent event who underwent surgery, controls are patients without a recurrent event who also underwent surgery. Cases and controls will be matched for [type of] surgery exposure. Four possible risk factors will be tested: 1. The presence of Factor V Leiden or non-O blood type or prothrombin mutation, 2. provoked or unprovoked first event, 3. DVT or PE as a first event and 4. sex. Odds ratios with 95% CIs will be calculated for these risk factors using logistic regression analysis. A prediction model will be developed if the number of cases is sufficient enough.

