| Neurosurgical                           |                    |                         |                                        |                          |                                       |
| Abdominal                               |                    |                         |                                        |                          |                                       |
| Minor abdominal                         |                    |                         |                                        |                          |                                       |
| Major abdominal                         |                    |                         |                                        |                          |                                       |
| Vascular                                |                    |                         |                                        |                          |                                       |
| Minor vascular                          |                    |                         |                                        |                          |                                       |
| Major vascular                          |                    |                         |                                        |                          |                                       |
| Non-orthopaedic day-care surgery |                    |                         |                                        |                          |                                       |
| VT recurrence risk                      | number of patients | 1-month
HR (95%CI)   | 3-month
HR adj * (95%CI) | 6-months
HR (95%CI)   | 1-year
HR adj * (95%CI) |
| No surgery                       |                    | ref                     | ref                                    | ref                      | ref                                   |
| Surgery (all)                    |                    |                         |                                        |                          |                                       |
| Orthopaedic surgery (all)        |                    |                         |                                        |                          |                                       |

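### Exposure includes procedures done because of the thrombosis, and same-day recurrences have no assignment rule, so some reversed events can count as post-surgical; the case-control study sets no time order at all

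*Protocol*

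**What the plan says.** Protocol section 2b sets the exposure: "We are interested in all surgical procedures (i.e. orthopedic, non-orthopedic, gynecological, urological, abdominal, vascular, neurosurgical, etc". Day-care and inpatient procedures both count, and the source is administrative: "These procedures are identified using ICD-coding that is registered in the CBS database". No code is excluded because of the reason for the procedure. The tables in section 4 give vascular surgery its own rows, including "Minor vascular".

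Section 3a sets the timing: "The time window of surgery exposure for each individual is defined as 3-months from the surgery date". The sensitivity analyses change how long the window is: "Therefore we will also consider a 1-month, 6-month and 1-year time window after surgery". Follow-up runs "until the end of follow-up (end of study, dead, recurrent event or loss to follow-up, whichever occurs first", and the model is specified as follows: "Cox-proportional hazards modeling (with a time-dependent co-variate [surgery]) will be used to calculate a hazard ratio for developing recurrence".

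For the nested case-control study, section 3a says: "Cases are patients with a recurrent event who underwent surgery, controls are patients without a recurrent event who also underwent surgery". Neither a time order nor a window is attached to that definition.

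Section 2a shows that the two dates come from different places. Surgery dates come from the national statistics database. Recurrence details come from questionnaires, anticoagulation clinics, physicians and death statistics.

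**The concern.** Some procedures are done because a clot is present or suspected. If they count as exposure, a patient whose recurrence led to the procedure can appear as a patient whose surgery was followed by a recurrence. Three features of the plan leave room for this.

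- The exposure definition does not look at the reason for the procedure.
- The window opens on the surgery date, with no rule for a recurrence carrying that date. The sensitivity analyses vary only the window's length, so they cannot expose a problem at its start. The shortest window concentrates it.
- The case definition in the case-control study asks only that a patient had both a recurrence and surgery.

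Few events are to be expected inside a short window, so a small number of reversed events could visibly move the hazard ratios. They would also raise the cumulative incidences that answer objective 1, which are meant to guide anticoagulant prescribing. In the case-control study, patients operated on after their recurrence would dilute the case group with recurrences unrelated to surgery. The risk factors found would then not be specific to the post-operative setting.

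**Working it through.** **Step 1. The plan's own figure.** Section 3b states a detectable relative risk of 1.6 at 80% power, with 10% exposed and 5% recurrence in the unexposed. I used the pooled-variance two-proportion formula with 473 exposed, 4258 unexposed and an assumed alpha of 0.05. The smallest detectable relative risk is 1.647 two-sided, or 1.598 one-sided with continuity correction. The stated figure is reproduced to its rounding. Nothing below depends on it; only the 10% is reused.

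**Step 2. Which events can be reversed, by date order.** This assumes a procedure prompted by the recurrence.

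| Recorded order | Cohort analyses (rates, cumulative incidence, Cox) | Case-control study |
|---|---|---|
| Procedure after recurrence | Cannot claim the event; follow-up has ended | Patient can qualify as a case |
| Same day | Not specified | Patient can qualify as a case |
| Procedure shortly before a late-recorded recurrence | Counts as exposed | Patient can qualify as a case |

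The same-day row can go either way. A literal reading of the window puts day 0 in exposed time, and a simple count of events in the window would follow it. The usual (start, stop] coding of a time-dependent covariate puts a same-day event in the preceding, unexposed interval. The plan's rates and its hazard ratios could therefore treat the same event differently.

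**Step 3. What one such event is worth.** The documents give no count of these events, so this is an illustration of leverage.

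Inputs:
- 4731 patients and 700 recurrences (section 3b)
- 10% exposed (section 3b, the plan's own working assumption)
- one operation per exposed patient (my assumption)
- mean follow-up 5 years, range 4 to 6 (my assumption; not in the protocol)
- the whole-cohort rate as the background rate (approximation)

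Calculation at 5 years:
- Background rate: 700 / (4731 × 5) = 700 / 23,655 = 0.0296 per person-year.
- Exposed time, 3-month window: 473 × 0.25 = 118 person-years.
- Expected exposed events at HR 1: 118 × 0.0296 = 3.5.
- Added to the HR by each reversed event: 1 / 3.5 = 0.29.
- 1-month window: 473 / 12 = 39.4 person-years, 1.17 expected events, and 1 / 1.17 = 0.86 per event.
- 30% exposed, 3-month window: 10.5 expected events, and 1 / 10.5 = 0.10 per event.

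| Mean follow-up (assumed) | Rate per 100 person-years | Expected events, 3 months, HR 1 | Added per event, 3 months | Added per event, 1 month |
|---|---|---|---|---|
| 4 years | 3.7 | 4.4 | 0.23 | 0.69 |
| 5 years | 3.0 | 3.5 | 0.29 | 0.86 |
| 6 years | 2.5 | 2.9 | 0.34 | 1.03 |

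Two reversed events would move a true HR of 1.6 to 1.6 + 2/3.5 = 2.2 (range 2.1 to 2.3), and a true HR of 3.0 to 3.6 (3.5 to 3.7).

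On the absolute scale, the 3-month risk at HR 1 is 3.5/473 = 0.74%, and each event adds 1/473 = 0.21 percentage points.

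**The case against.** The strongest reply is that the plan already deals with the ordinary form of reverse causation. A reader might infer from section 2b that any procedure prompted by a recurrence counts as exposure, because no sentence requires surgery to come first. For the cohort analyses that does not hold. Follow-up stops at the recurrence and surgery enters as a time-dependent covariate, so a later procedure adds no exposed time. A reader might also infer that same-day recurrences are declared exposed, or labelled as caused by surgery. The protocol does neither: it is silent on day 0, it describes the sensitivity windows as running after surgery, and it estimates risks and hazard ratios without attributing single events. These limits stand.

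Second, code lists and the handling of ties are often left to an analysis plan, and none is shown. That is fair for the day-0 convention alone. It does not cover the rest: the protocol itself defines the exposure, the start of the window and the case, and as written these definitions admit VT-indicated procedures.

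Third, nothing in the protocol shows that such procedures are registered among the surgical codes, that they fall in the vascular rows, or that any occurred in this cohort. The number of reversed events is therefore unknown. If the true effect is large, one event matters less: at HR 3.0 it gives about 3.3, a change of under 10%. Section 3b also concedes that the exposure frequency is unknown, and at 30% exposed the shift is about 0.10 per event. All of this stands, and it is why the figures above describe leverage and do not estimate a bias.

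Finally, the case-control study lies within the cohort, so one could assume that it inherits the end of follow-up. The text does not say so, and the case definition carries no date condition.

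**Conclusion.** The point holds in a limited form. VT-indicated procedures are not excluded from exposure, and same-day recurrences are not assigned. In the cohort analyses the open route is confined to procedures dated on the day of the recurrence, or shortly before a recurrence recorded late. The separate sources of the two dates make the second possible, but the protocol does not show that it occurs. The case-control study is the more exposed part, since an operation at any time after the recurrence fits its case definition.

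The size of any bias cannot be computed from the protocol. With 10% exposed, one operation each and a mean follow-up of 4 to 6 years, each reversed event would add 0.23 to 0.34 to the 3-month hazard ratio and 0.69 to 1.03 to the 1-month one. With 30% exposed and 5 years, the 3-month figure falls to about 0.10. This is enough leverage to justify an inexpensive correction. It is not evidence that the planned hazard ratios will be wrong.

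**What to change.** 1. **Section 2b.** Exclude from exposure a list of procedure codes whose purpose is to treat or diagnose VT. Since the protocol says that the linkage to the surgery data has been made, fix the list before procedure codes are compared with recurrence dates. Only this change also covers recurrences recorded a day or two late; a date rule alone does not.
2. **Section 3a, cohort analyses.** Start exposed time on the day after surgery. Assign a recurrence dated on the surgery day to unexposed time, in the same way for rates, cumulative incidences and the Cox model. Add one sensitivity analysis that counts day 0 as exposed.
3. **Section 3a, case-control study.** Require that a case's surgery precedes the recurrence and that the recurrence falls within the exposure window.

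The cost is a code list and date rules applied to data already held. The downside is that a few true same-day post-operative recurrences move to unexposed time; the day-0 sensitivity analysis shows how much that matters.

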### **c. Outcome (dependent variable)**

The outcome of interest is recurrent VT. In the MEGA follow-up study, events are identified as certain and uncertain recurrences. For our study we will consider certain recurrences only and censor follow-up time in case a non-certain recurrent event has occurred. In addition, uncertain cases will be included as recurrent events in a sensitivity analysis.

### **d. Confounding factors and selection bias**

#### *Confounding*

Lots of acquired risk factors can confound the association between surgery and recurrent venous thrombosis. Patients in the MEGA study completed a questionnaire on putative risk factors for a first VT, also, later in the follow-up study, about half of the participants completed a second questionnaire on risk factors for a recurrent VT. We will adjust for baseline factors including age, sex,

body mass index (BMI), and chronic diseases such as liver and kidney failure and inflammatory diseases (including rheumatoid arthritis) (full definition of chronic and inflammatory disease in MEGA are provided in Ocak et al. JTH 2013 and [name] et al. PLOS Med 2015). We will impute data when data on one of these confounders are missing. Patients with cancer (at baseline and during follow-up) will be excluded from all analyses.

There are no data available on thromboprophylactic therapy during or after surgery. All guidelines advise to give prophylactic (low dose) anticoagulant therapy during surgery for patients with a history of VT. Therefore we assume that this has been the case for all patients who underwent surgery.

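### Removing patients who develop cancer during follow-up from all analyses conditions the cohort on a future event, so the absolute risks and rates describe a group that cannot be identified at surgery

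*Protocol*

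**What the plan says.** The rule is in section 2d of the protocol, under Confounding: "Patients with cancer (at baseline and during follow-up) will be excluded from all analyses". That paragraph opens with the premise that "Lots of acquired risk factors can confound the association between surgery and recurrent venous thrombosis", so the plan evidently treats cancer as related to both surgery and recurrence.

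Section 3a starts the main follow-up "from stop date anticoagulant treatment after first VT" and ends it at "end of study, dead, recurrent event or loss to follow-up, whichever occurs first". A cancer that arises later is unknown at that start date, and also at the date of the first thrombosis, which is the alternative start. The exposure is broad ("We are interested in all surgical procedures", section 2b). The planned quantities are cumulative incidences after surgery, "incidence rates by dividing the number of events by person-time for the exposed and the unexposed time periods", and a Cox model with surgery as a time-dependent covariate.

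Section 2c treats another post-baseline event differently: an uncertain recurrence censors follow-up when it occurs. The selection-bias paragraph of section 2d covers only questionnaire non-response and linkage to the surgery register. The protocol neither defends exclusion on a later cancer nor plans a sensitivity analysis for it.

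**The concern.** Baseline cancer is a legitimate entry criterion because it is known when follow-up begins. Later cancer is not. A patient diagnosed four years after stopping anticoagulation contributes four cancer-free years, perhaps an operation and perhaps a recurrence, and the rule deletes all of it. The plan otherwise respects time order, since surgery is time-dependent and uncertain recurrences are censored as they happen.

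Objective 1 is an absolute risk intended to guide prescribing around surgery. A risk computed among patients who will remain free of cancer cannot be applied at the operation, because membership of that group is decided afterwards. The nested case-control study is drawn from the same cohort and inherits the selection.

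The sentence is also ambiguous, because follow-up ends at recurrence. Cancer during follow-up may therefore mean cancer before recurrence or censoring, or it may mean any cancer up to the end of the study. The first reading removes only patients who were event-free up to their cancer. The second also removes recurrences that preceded a cancer diagnosis.

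**Working it through.** The protocol states no figure on this point, so there is none to reproduce. It gives no cancer incidence and no overlap of cancer with surgery. All cancer inputs below are assumptions.

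**Step 1. Only cancer before recurrence or end of follow-up counts; cancer independent of recurrence.**

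Assumed inputs: recurrence hazard L = 0.03 per year, cancer hazard m = 0.005 to 0.02 per year, follow-up tau = 5 to 7 years. A patient is kept if cancer comes later than the earlier of recurrence and tau. Put a = L + m and S = exp(-a·tau). Per enrolled patient:

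- events kept: E = (L/a)(1 - S)
- person-years kept: P = L[1 - S(1 + a·tau)]/a² + tau·S
- rate as section 3a computes it: E/P, to be compared with L

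| m | tau | S | E | P | E/P | ratio to L |
|---|---|---|---|---|---|---|
| 0.005 | 5 | 0.8395 | 0.13761 | 4.5313 | 0.03037 | 1.012 |
| 0.01 | 5 | 0.8187 | 0.13595 | 4.4222 | 0.03074 | 1.025 |
| 0.02 | 7 | 0.7047 | 0.17719 | 5.5169 | 0.03212 | 1.071 |

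The planned rate is therefore inflated by about 1.2%, 2.5% and 7.1%. The hazard at time zero is inflated more, by 1/(E + S) = 1.023, 1.047 and 1.134, but that is the peak. The distortion falls to nothing at tau, and the plan reports averages over person-time.

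**Step 2. Cancer linked to surgery and recurrence (simulation, 1,000,000 patients per scenario).**

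Assumed throughout: 6 years of follow-up, recurrence 3 per 100 person-years, surgery hazard 0.05 per year, true hazard ratio 3 in a 3-month window. In the first three rows, recurrence hazard is tripled from 0.5 year before diagnosis, and half of cancers have surgery 0.1 year before diagnosis. The fourth row uses a fivefold hazard from 1 year before diagnosis and surgery 0.15 year before diagnosis in 70%. The last row has no link. Each cell gives exposed rate / unexposed rate per 100 person-years, then the rate ratio.

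| Cancer per 100 person-years | Censor at diagnosis | Exclude any cancer by study end | Exclude cancer before recurrence or end |
|---|---|---|---|
| 0.5 | 9.39 / 3.00, 3.13 | 8.98 / 2.99, 3.01 | 9.73 / 3.04, 3.20 |
| 1 | 9.79 / 3.02, 3.24 | 8.97 / 2.99, 3.00 | 10.51 / 3.10, 3.39 |
| 2 | 10.28 / 3.06, 3.36 | 8.75 / 3.01, 2.91 | 11.86 / 3.23, 3.67 |
| 2, strong link | 14.97 / 3.21, 4.66 | 9.28 / 3.02, 3.07 | 18.33 / 3.37, 5.44 |
| 2, no link | 8.94 / 3.02, 2.96 | 8.95 / 3.01, 2.97 | 9.49 / 3.20, 2.97 |

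Against censoring at diagnosis, in the linked rows:

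- Study-end reading: the exposed rate is lower by 4% (8.98/9.39 = 0.956) to 38% (9.28/14.97 = 0.620).
- Before-recurrence reading: the exposed rate is higher by 4% (9.73/9.39 = 1.036) to 22% (18.33/14.97 = 1.224).

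With no link, the rate ratio does not move under either reading, but the before-recurrence reading still raises both rates by about 6% (9.49/8.94 = 1.062; 3.20/3.02 = 1.060).

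**The case against.** The strongest defence is that the exclusion is there to remove confounding, and that for the hazard ratio it may do so better than censoring. Surgery performed for a still-undiagnosed cancer, and a recurrence caused by it, both stay in the data if follow-up is merely censored at diagnosis. In the linked scenarios the true cancer-free hazard ratio was 3. Exclusion up to study end gave 2.91 to 3.07, while censoring gave 3.13 to 4.66. This part of the defence stands. Censoring suits the absolute risk but is not clearly better for the hazard ratio, so any fix must deal with surgery shortly before diagnosis. The defence does not rescue the rule for Objective 1, nor does it settle which reading applies.

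Three stronger readings are tempting and are not supported:

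- A reader might infer that the hazard ratio is biased upwards. If 5-10% of unexposed recurrences led to a cancer diagnosis and few post-surgical ones did, the study-end reading would inflate it by 1/0.95 = 1.05 to 1/0.90 = 1.11. The protocol gives no such percentages, operations also reveal cancer, and the linked simulations under the same reading moved the ratio down (3.24 to 3.00 at 1 per 100 person-years). No sign can be claimed.
- A reader might take the time-zero inflation of 2-13% as the size of the problem. That is a peak. The planned rate moves by about 1-7% under the same assumptions.
- A reader might count the absence of cancer from the end-of-follow-up list in section 3a as a second error. Under the present rule those patients are already gone, and the list is not exhaustive in any case, since it also omits the uncertain recurrences that section 2c censors. The list needs changing only because the fix requires it.

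It is also fair to say that the distortion is small if incident cancer is rare, and that the protocol does not state how follow-up cancer is ascertained.

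**Conclusion.** The point holds for the absolute risks and rates. The rule selects patients on what happens after time zero, and nothing else in the protocol repairs it. The resulting estimates apply to patients who will stay cancer-free, and the wording admits two readings that can push the rates in opposite directions.

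Size and direction cannot be fixed from the protocol. With independence, cancer at 0.5-2% per year, 5-7 years of follow-up and exclusion only for cancer before recurrence or end of follow-up, the average rate is about 1-7% too high and the rate ratio is unchanged. With cancer linked to surgery and recurrence, rates and hazard ratio can move either way. The larger simulated shifts depend entirely on the assumed strength of that link and illustrate sensitivity, not an expected bias. The rule should be changed before analysis because it touches every planned estimate.

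**What to change.** In section 2d, exclude only patients with cancer present at or before the start of follow-up. For cancer diagnosed later, keep the person-time, operations and recurrences before diagnosis and censor at the diagnosis date. Add that date to the events that end follow-up in section 3a.

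Add two sensitivity analyses:

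- One that handles surgery shortly before a cancer diagnosis, for example by leaving out exposure windows in which cancer is diagnosed. This addresses the confounding by undiagnosed cancer that censoring leaves in the hazard ratio.
- The present full exclusion, with a statement of whether cancer found after a recurrence counts.

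The wording change is small. The real cost is obtaining diagnosis dates for patients already identified as having cancer; the protocol does not say whether these dates are available. Some residual confounding by occult cancer will remain and should be acknowledged when the hazard ratios are reported.
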